### 2.5. Community Advisory Board Assessments

The *Wilder Collaboration Inventory* is a tool that measures the collaboration between and within groups that represent multiple interests using 40 questions reflecting twenty dimensions: (1) history of collaboration or cooperation in the community; (2) collaborative group seen as a legitimate leader in the community; (3) favorable political and social climate; (4) mutual respect, understanding, and trust; (5) appropriate cross-section of members; (6) members see collaboration as in their self-interest; (7) ability to compromise; (8) members share a stake in both process and outcomes; (9) multiple layers of participation; (10) flexibility; (11) development of clear roles and policy guidelines; (12) adaptability; (13) appropriate pace of development; (14) open and frequent communication; (15) established informal relationships and communication links; (16) concrete, attainable goals and objectives; (17) shared vision; (18) unique purpose; (19) sufficient funds, staff, materials, and time; and (20) skilled leadership [38]. The twenty dimensions can also be summarized as collaborative purpose, member characteristics, communication, process/structure, and environment or resources. At the end of each 1-year term of service, CAB members rate how much they agree or disagree with each of 40 statements on a 5-point Likert-type scale. Scores are averaged across all board members and evaluated according to standards set by the measurement development team. Specifically, an average score above 4.0 demonstrates strong collaboration, averages of 3.0–3.9 are borderline scores, and average scores of 2.9 or below are areas of concern [39]. Following each year, data will be reviewed from this assessment to modify the CAB processes and protocols as needed.

### 2.6. Teacher Assessments

In the *SAGE Teacher Self Evaluation Questionnaire*, an assessment specifically developed for SAGE, teachers rate themselves on how often and how well they complete the PRIME principles when delivering SAGE. Teachers respond to three to five items for each principle (20 items total) using a four-point rating scale of never, rarely, sometimes, or always. Scores are then averaged across all questions within each PRIME principle. At the end of the survey is a section where teachers can write down any topics or areas on which they would such as technical assistance. This questionnaire is filled out during weeks 3 and 10 of SAGE. Week three responses are used to tailor the booster training session to teacher’s specified needs, and week 10 responses help SAGE staff to provide ongoing technical assistance that can enhance sustainability.

The *Teacher Program Sustainability Survey* is based on an existing tool and measures factors associated with program sustainability that are especially associated with the parent-teacher interaction [40]. This 14-item survey is completed once before SAGE starts and once again following delivery of the SAGE curriculum. Questions focus on the types, frequency, and direction of communication between parents and teachers. The survey also specifically asks about parent-teacher communication related to children’s physical activity and nutrition behaviors. Responses from baseline to post-intervention can be compared to evaluate intervention related changes in parent-teacher communication.

### 2.7. Teacher and Director Assessments

*SAGE Self Efficacy Assessment* is an assessment specifically developed for SAGE that is administered to teachers and directors at the teacher training (two to three weeks before start date), the end of the “see one” phase of SAGE (week 5), at the end of the “do one” phase of SAGE (week 10), and following program delivery. This questionnaire includes five statements that staff respond to using a five-point Likert-type scale: (1) strongly disagree, (2) disagree, (3) neither agree or disagree, (4) agree, and (5) strongly agree. Statements ask how confident staff are that they continue to care for and maintain the garden, allow children to water and interact with the garden weekly, provide children with active songs, games, and discussions from the SAGE curriculum weekly, provide children with the mindful eating experience with fresh fruits and vegetables weekly, and engage parents and other community members in SAGE. Averages across all five questions are calculated by staff type (i.e., director vs. teachers) and for each ECEC. Changes or patterns in self-efficacy will be tested to determine whether they mediate changes in other sustainability constructs (e.g., ECEC health environments).

*Interviews.* Exit interviews with ECEC directors, teachers, and other engaged staff (e.g., kitchen personnel, teacher aids) will be conducted after implementation has been completed to investigate factors impacting sustainability along the dimensions of child learning, teacher acquisition of skills needed to deliver the SAGE curriculum, and ECEC achievement of policy guidelines and project milestones. Interview data can be used to inform scaling up SAGE for broader deployment if it is successful in meeting its goals or modifying SAGE if some pieces are unsuccessful. Semi-structured interviews are iterative in nature, taped, transcribed, and analyzed using thematic content analysis. Emergent themes will be identified using a constant comparison approach [41,42,43,44].

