### 2.2. Sustainability Action Plan (SAP) Strategies

The SAP incorporates strategies that encourage community members, ECEC teachers, ECEC directors, and parents to engage with SAGE to help create buy-in, improve program delivery, and develop sustainable processes that improve the ability of the ECEC to maintain SAGE. Strategies were developed to engage each stakeholder group (Figure 1). Processes were created on build and maintain the garden, engage all groups and foster coordination, collaboration, and cooperation between them, to enhance behavioral persistence [37], and in turn, sustainability [2].

*Community Advisory Board Meetings.* The SAGE CAB membership, roles, and responsibilities have been previously described [34,35]. In the context of sustainability, the CAB serves as an important resource and sounding board for SAGE. The SAGE CAB for the SAP comprises local community leaders who represent gardening, early childcare, local and state government, and health communities. The CAB and the scientific team identify and implement short-term and long-term goals for the SAP in bi-monthly meetings. CAB members are paid a modest honorarium of $100 annually, and the chair, $200. The CAB provides important information about community capacity and serves as a bridge between the scientific team and community. Each CAB member serves a one-year term at the end of which, the member is given the opportunity to rotate off or continue for an additional term.

*Adaptive Curriculum Delivery Approach.* The SAGE curriculum will be introduced using a continuous one-hour format two times per week for 12 weeks. However, activities may be completed sequentially or re-ordered, offered all in one go, or throughout the school day to fit different teaching styles and classroom schedules. Moreover, activities may be offered indoors or outdoors to accommodate bad weather (e.g., excessive heat).

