*Teacher Training and Technical Support.* Another part of curriculum delivery that promotes sustainability is the use of a “see one, do one, teach one” teacher training method that has been used in health care delivery. The first 12 sessions will be led by the research team over six weeks, with teachers observing and assisting in SAGE delivery. Gradually, teachers will begin to lead portions of sessions during this time. Then, the 12 sessions can be repeated over a second six-week period and led by the teachers with assistance from the research team. Teachers will complete a 90-min training session prior to beginning implementation and a 30-min booster session about five weeks into implementation. Trainings focus on five PRIME principles that reinforce best practices for delivering SAGE: *P*romote positive experiences, *R*oom management, *I*mprovement directed reinforcement, *M*odeling appropriate behaviors, and *E*stablishing garden maintenance. On-demand technical support will be available throughout the study for ECECs and teachers who desire additional help.

*Action Planning Meetings with Directors.* Over the course of the SAGE program, research staff will meet three times for one hour with ECEC directors to develop a plan for institutionalizing SAGE and sustaining it beyond the funding period. ECEC directors will also complete assessments to evaluate resources, barriers, and facilitators for sustaining SAGE. In the first meeting, directors will complete a self-assessment of their ECEC, be given the opportunity to ask questions or voice concerns about SAGE, and prompted to think about long-term sustainability. In the second meeting, after they have more experience with SAGE, directors will review the results from their assessments, discuss how their results compare to other ECECs, and develop an action plan and set goals for improving low-scoring areas. Each action plan will be discussed with the CAB to identify community resources to support each ECEC director’s goals and provide feedback. In the final meeting of the semester, SAGE staff and directors will discuss progress towards achieving their goals, reevaluate and set new goals as needed, and complete assessments a second time.

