### 2.4. SAGE SAP Sources of Data

To evaluate the impact of the strategies on each CORD construct and at each level of the EMO, a battery of measures designed to include perspectives and reflect priorities of each stakeholder will be administered. A summary, organized by sustainability construct, is presented in Table 1. At the micro level, teacher exit interviews and ECEC directors surveys are conducted, along with on-site environmental surveys (NAP SACC, PARA), and which are to be triangulated with extensive field notes during implementation. The Wilder Collaboration Factors Inventory is completed annually with our community advisory board. At the meso-level, in addition to relying on teacher interviews, teachers complete a questionnaire, and parents complete a brief survey. Teacher surveys inform the ex0 level. At the macro level, meeting minutes, environmental assessment, and CAB measures will be examined.

To maximize understanding of the efficacy of the SAP, information will be collected from all stakeholders. CAB members will complete a survey evaluating their role with the collaboration. Teachers will complete self-evaluations of their ability to implement SAGE, score parent-teacher interactions that may affect sustainability, rate their self-efficacy for sustaining SAGE beyond the funding period, provide reflections on SAGE implementation after each session that are recorded in field notes, and participate in post-intervention interviews. ECEC will directors evaluate factors associated with program sustainability related to ECEC administration, policies, and procedures, rate how SAGE has impacted their site, score their self-efficacy for sustaining SAGE beyond the funding period, and participate in post-intervention interviews. Parents will complete surveys evaluating the newsletters and rating their interaction [33]. SAGE staff, in coordination with ECEC teachers and directors, will complete assessments to evaluate the physical activity and nutrition environment at the ECEC, as well as record meeting minutes of all meetings with CAB members, ECEC teachers, and ECEC directors. The timing of each assessment is presented in Table 2.

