### 2.8. Director Assessments

The *Director Program Sustainability Survey* is based on an existing tool [40] and measures factors associated with program sustainability including ECEC administration, policies, and procedures. Specifically, questions focus on the type of ECEC (e.g., for-profit vs. non-profit), the number, types, processes, and rules for meals served at the ECEC; current physical activity and nutrition training offered to staff at the ECEC as well as future training needs; use of best practices for physical activity and nutrition at the ECEC as well as barriers/facilitators to using those practices; and ECEC directors’ communication with parents. Directors complete this survey prior to and following implementation of SAGE. The 38 questions on this survey consist of check-all that apply, multiple choice, fill in the blanks, and Likert-type scale questions. Responses from baseline to post-intervention will be compared to evaluate the impact of the SAP on outcomes.

The *Sustainability Needs Assessment* (SNA) is based on an existing tool [1] and completed by the ECEC director during SAGE week 3 and SAGE week 10. This assessment allows the director to rate the SAGE program on five RE-AIM dimensions: reach, efficacy, adoption, implementation, and maintenance [45]. Each RE-AIM dimension is evaluated using 6–10 questions (37 total), which are scored using a five-point Likert-type scale: (1) strongly disagree, (2) disagree, (3) neither agree or disagree, (4) agree, and (5) strongly agree. The SNA also investigates process factors associated with implementing the new program such as the perceived feasibility of the study design, the center setting, and the community environment (e.g., having the space and resources available to support the program). Responses from baseline to post-intervention will be compared to evaluate the impact of the SAP on SAGE’s perceived RE-AIM characteristics.

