**Figure 2 ijerph-19-05511-f002:**
[figure not shown]
The SAGE SAP steps rollout process and measures by stakeholder.

**Table 1 ijerph-19-05511-t001:** Measures for Evaluating the SAP by Ecologic Model of Obesity (EMO) Level and Sustainability Construct.

EMO Levels	CORD Sustainability Constructs			
	Replicability (repeatability, adaptability, expandability)	Continuation of Benefits (continued infrastructure and resources)	Institutionalization (policies and organizational structures)	Community Capacity (collaboration, community commitment, resource access)
Micro level	Teacher interviews Director Program Sustainability Survey Teacher Self-efficacy Assessment Field notes	Director Program Sustainability Survey Teacher Self-efficacy Assessment Meeting minutes Field notes	NAP SACC PARA Director Program Sustainability Survey Teacher Self-efficacy Assessment Sustainability Needs Assessment	Wilder Collaboration Factors Inventory Sustainability Needs Assessment
Meso level	Teacher interviews SAGE Teacher Self Evaluation Questionnaire	Teacher interviews SAGE Teacher Self Evaluation Questionnaire Parent newsletter survey	N/A	N/A
Exo level	Teacher Program Sustainability Survey Teacher Self-efficacy Assessment	Teacher Program Sustainability Survey Teacher Self-efficacy Assessment	N/A	N/A
Macro level	Meeting minutes	Meeting minutes	NAP SACC	Wilder Collaboration Factors Inventory

Note. NAP SACC, Nutrition and Physical Activity Self-Assessment for Child Care; PARA, Physical Activity Resource Assessment.

**Table 2 ijerph-19-05511-t002:** Timing of SAP Assessments.

	Baseline	Week 3	Week 5	Week 10	Post-Intervention
*Community Advisory Board*					
Wilder Collaboration Inventory					X
*Teachers*					
Self-Evaluation		X		X	
Teacher Survey	X				X
SAGE Reflections		X	X	X	
*Directors and Teachers*					
Self-efficacy	X		X	X	X
Interviews				X	
*Directors*					
Director Survey	X			X	X
Sustainability Needs Assessment		X		X	
*Parents*					
Newsletter Survey					X
*Environmental Assessments*					
PARA	X				X
NAP SAC	X				X
*Other Measures*					
Field/Meeting Notes	X	X	X	X	X
Cost to Deliver					X

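### Table 2 places the exit interviews and an extra director survey at week 10, against the text, and the week-5 and week-10 phase labels are not reconciled with the six-week blocks

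*Protocol article*

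**What the plan says.** **Delivery.** Section 2.2 introduces the curriculum in a "continuous one-hour format two times per week for 12 weeks". Its paragraph on teacher training describes two blocks: "The first 12 sessions will be led by the research team over six weeks, with teachers observing and assisting in SAGE delivery", after which "the 12 sessions can be repeated over a second six-week period and led by the teachers", with help from the research team. The same paragraph names a three-part training method (see one, do one, teach one) and puts a booster session about five weeks in.

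**Exit interviews.** Section 2.7 says that they "will be conducted after implementation has been completed to investigate factors impacting sustainability". Section 2.4 calls them post-intervention for teachers and again for directors. In Table 2 ("Timing of SAP Assessments") the only mark in the Interviews row is under Week 10, and the Post-Intervention cell is empty.

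**Director survey.** Section 2.8: "Directors complete this survey prior to and following implementation of SAGE". Table 2 marks it at Baseline, Week 10 and Post-Intervention.

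**Self-efficacy.** Section 2.7 schedules the form at the teacher training, at the end of see-one (week 5), and at the end of the do-one "phase of SAGE (week 10), and following program delivery".

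**Rollout.** Section 2.3 places the booster, and with it the switch from see-one to do-one, in Step 3 (weeks 4 to 5). It dates Step 4 to weeks 5 to 10, and then speaks of assessments at the end of Step 4 and of the 12-week intervention in one phrase.

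**The concern.** The article's second stated aim is to describe the evaluation plan, and Table 2 is the schedule that a site would follow. For the interviews, the schedule and the text cannot both be followed. An exit interview held at week 10 takes place while teachers are still delivering the programme, so it cannot cover the last sessions or the close of delivery. Section 2.7 intends these interviews to inform scale-up or modification of the programme, and the last weeks of teacher-led delivery bear on that.

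The director survey raises a smaller question: whether there are two administrations or three.

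The phase labels matter because they tell the reader what the week-5 and week-10 self-efficacy scores represent. If see-one and do-one are the two six-week blocks, neither score is taken at the end of its phase. Section 2.3 has the process repeated six times over three cohorts, so an unclear schedule also leaves room for the timing to differ between cohorts.

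**Working it through.** **Is the table read correctly?** The tables were extracted by a program, so the column positions need a check. The Self-efficacy row has marks at Baseline, Week 5, Week 10 and Post-Intervention, which are the four occasions in section 2.7. The Self-Evaluation row (weeks 3 and 10) agrees with section 2.6, and the Sustainability Needs Assessment row (weeks 3 and 10) agrees with section 2.8. The columns line up, so the Interviews and Director Survey marks can be taken as printed.

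**Interviews.** Inputs from section 2.2: 2 sessions a week and 12 weeks.

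- Total sessions: 2 × 12 = 24.
- Delivered by the end of week 10: 2 × 10 = 20.
- Remaining: 24 − 20 = 4, which is 4/24, or about 17% of the programme, over 12 − 10 = 2 weeks.
- If the interview fell at the start of week 10, 2 × 9 = 18 sessions would have been delivered and 6 would remain. Four is therefore the smallest shortfall at the stated pace.

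**Director survey.** No arithmetic applies. Section 2.8 gives two occasions and Table 2 gives three. The baseline to post-intervention comparison planned in section 2.8 can be made either way. Only the status of the week-10 administration is unclear.

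**Phase labels.** Inputs from section 2.2: two blocks of 12 sessions at 2 a week.

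| | Length | Block ends | Label in section 2.7 | Gap |
|---|---|---|---|---|
| First block, research team leads | 12 / 2 = 6 weeks | week 6 | end of see-one, week 5 | 1 week, 2 sessions |
| Second block, teachers lead | 12 / 2 = 6 weeks | 6 + 6 = week 12 | end of do-one, week 10 | 2 weeks, 4 sessions |

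The stated weeks 5 and 10 were then tried under other conventions:

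- Counting weeks from 0, the blocks end in weeks 5 and 11. This gives the first label but not the second.
- Two five-week phases would need 12 / 5 = 2.4 sessions a week and a 10-week programme, against the stated 2 a week and 12 weeks.
- If see-one ends at the booster (weeks 4 to 5 in section 2.3), do-one fills the Step 4 window (weeks 5 to 10) and a teach-one phase takes weeks 11 and 12, then both labels fit. However, the article never dates a teach-one phase, and these phases would not coincide with the two leadership blocks.

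The labels can thus be explained only by a division of the 12 weeks that the article does not set out.

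**Step 4.** Its heading ends it at week 10. The later sentence mentions its end together with the end of a 12-week intervention. If these are one time point, the two statements are 2 weeks apart. If they are two, the sentence refers to week 10 and post-intervention, both of which are columns in Table 2.

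**The case against.** The strongest objection is that the phase labels are not an arithmetic slip. Section 2.2 never calls its two blocks see-one and do-one, names a three-part method, and has teachers gradually leading portions of sessions during the first block. Section 2.3 puts the switch to do-one at the booster, so week 5 appears consistently as a switch point. Section 2.7 also lists the time after programme delivery separately from the end of do-one. This stands. A reader might infer that the plan has miscounted and that the phases must end at weeks 6 and 12, but the article does not say so. What remains is that the labels and the blocks are left unreconciled.

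The Step 4 sentence can likewise be read as naming two time points, so it is an ambiguity to clear up and not a firm contradiction.

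Three stronger readings are tempting and are not supported:

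- *That Table 2 restricts teacher reflections to a few sessions, because it marks them only at weeks 3, 5 and 10.* Section 2.4 says that teachers "provide reflections on SAGE implementation after each session that are recorded in field notes". The field-notes row is marked in every column, and a grid of five columns cannot show 24 sessions. The row is compatible with the text.
- *That the mediation analysis would use the wrong exposure.* Section 2.7 says only that changes or patterns in self-efficacy will be tested as mediators. It specifies no contrast by phase, and the four measurements remain usable whatever weeks 5 and 10 are called.
- *That the week-5 form must precede the booster.* The article fixes no order within that week.

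For the interviews, it can be said that two consistent statements in the text would prevail over one table cell, so that no harm follows. This is plausible, but the table is the operational schedule and nothing in the article says which source governs.

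**Conclusion.** The point holds as a minor inconsistency in the assessment schedule.

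- **Interviews:** a direct conflict between Table 2 and sections 2.4 and 2.7. Following the table would put the exit interviews about two weeks, and at least 4 of 24 sessions, before delivery ends. This assumes delivery at the stated pace of two sessions a week for 12 weeks, with the table's weeks counted from the start of the programme.
- **Director survey:** a direct conflict, with three administrations in Table 2 and two in section 2.8.
- **Phase labels and Step 4:** unclear and unreconciled with blocks that end at weeks 6 and 12. The gaps of one and two weeks count as discrepancies only if the blocks are the phases, which section 2.3 suggests (the switch is when teachers start to become the main implementers) but the article does not state.

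Sample size and error rates are not affected. The practical consequence is the timing of the interview data meant to inform scale-up, and what the week-5 and week-10 self-efficacy scores may be said to represent.

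**What to change.** 1. In Table 2, move the Interviews mark from Week 10 to Post-Intervention, in line with sections 2.4 and 2.7.
2. Make the director-survey time points agree: remove the Week 10 mark or, if a week-10 administration is intended, add it to section 2.8 with its purpose.
3. In section 2.7, either state which weeks make up see-one, do-one and any teach-one phase and how these relate to the two six-week blocks, or describe the two self-efficacy measures simply as week 5 and week 10.
4. In section 2.3, say whether the end of Step 4 and the end of the 12-week intervention are one time point or two.

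The cost is a few edits to Table 2 and to sections 2.3, 2.7 and, if needed, 2.8. No assessment is added.
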